### Approach for aim 3: evaluate MTurk as a cost- and time-efficient data collection method

Starting in Year 2, the MTurk platform will be used to collect data in support of the work conducted in Aims 1 and 2. The existing datasets contain the key measures of interest and are large enough to power initial analyses. However, they do not include the broad array of measures that might be useful, and none were intended to be representative of all CLBP patients. For example, the CERC dataset only includes CLBP and CNP patients currently being treated by a chiropractor, and the ACT sample only includes Active Duty military who were chiropractic clinical trial participants. The addition of MTurk data will be used to validate the relationships estimated on the existing datasets to see whether these estimates hold up in other samples, and allow additional measures to be included and tested for relevance before we move to the nationally representative KnowledgePanel sample for final evaluation. The KnowledgePanel data collection will replicate measures and participant characteristics captured in the new MTurk data. Therefore, we can evaluate the utility of the MTurk platform by comparing those data to the nationally representative sample from KnowledgePanel.

The new MTurk data collection will include chronic pain measures not previously concurrently collected in the other existing datasets (e.g., both the ODI and RMDQ) and will capture these measures in broader chronic pain populations. For example, a number of studies now indicate the importance of patient catastrophizing on chronic pain outcomes [69–72], and that the benefits of certain therapies are affected by changes in catastrophizing [73–77]. Catastrophizing is included in the CERC and existing MTurk datasets, however, a more detailed analysis of its effects related to the RMDQ might be desired. Also, the Graded Chronic Pain Scale [21] is not included in our existing datasets and given its extensive use it would be good to compare its grades to the ISS scores seen. Finally, patients’ retrospective rating of change, used in test-retest reliability and the sensitivity of measures to change, is captured in the ACT data, but not in the CERC or existing MTurk data.

The MTurk platform provides the opportunity to draw samples from different subgroups with different chronic pain conditions, using any set of items and over any time interval. The process for obtaining survey data via the MTurk platform is as follows: The MTurk surveys will be designed using SelectSurvey and then posted on the MTurk platform. MTurk participants who consent will first be administered a survey eliciting demographic information, their health conditions from a general health checklist, and the PROMIS-29. All respondents will receive $1 for this initial health screening survey. MTurk participants who endorse CLBP will be invited to answer additional questions including the ODI, RMDQ, and/or any other legacy measures of interest, for a “bonus” of $1.50. We will also employ MTurk to collect longitudinal data, which has been shown to be feasible in other studies (pilot data had an 80% response rate for second round data) [78]. MTurk participants are anonymous, but an intermediary platform (TurkPrime) allows the inclusion or exclusion of previous participants in new surveys. This can be done through various options including limiting survey responses to single respondents, or by sending emails to anonymous MTurk participants via the platform [79]. We plan to recruit participants for longitudinal data collection by emailing them survey links through their MTurk accounts using unique MTurk Worker IDs. They can view the survey announcement and participate if they choose. Respondents remain anonymous throughout this process.

In this study we will measure data quality, leveraging lessons from previous studies [80]. For example, to increase truthfulness of the anonymous respondents, we employ a two-tiered survey process by posting the surveys as “Brief Health Surveys” and piping respondents over to the full survey with bonus only if they endorse the conditions of interest. This reduces the likelihood of respondents simply endorsing CLBP to get paid to answer a survey on that condition [81]. To reduce selection bias, we will deploy small batches of surveys hourly throughout a several-week time period. This ensures sampling from individuals who are online at different times throughout the day and available on different days. We will implement attention checks to ensure the respondents are people and not robots, and to ensure respondents are paying attention. We will especially track meta-data such as time to complete each question and the survey, and missing data for the key measures of interest (PROMIS, ODI, RMDQ, and other legacy measures). Finally, MTurk participant user forums (i.e., Turkopticon) will be monitored for potential chatter related to the study.

In addition to providing a rich dataset to enhance the analyses performed for Aims 1 and 2 on existing data, we will compare the MTurk data to that gathered through KnowledgePanel. We will compare the cost and time to complete surveys, data quality, response at follow-up, relationships (correlations) seen between key variables, and sample representativeness in terms of demographics, duration of pain, proportions with different levels of the ISS, and PROMIS-29 scale scores. For data quality, we will include the same attention checks in the KnowledgePanel survey as are included in the MTurk survey and compare percentage of failures across datasets using χ^2^. The response rate at 3-month follow-up will also be compared using χ^2^. We will calculate and compare Spearman rank-order and product-moment correlations between key variables across data sources, and we will compare outcome effect sizes. Student’s t-tests will be used for continuous outcome and demographic variables. Effect sizes for each parametric test will be calculated with Cohen’s *d*. Chi-square tests of independence will be used with nominal independent variables, non-scalar dependent variables of categorical outcomes, and demographics variables. Chi-square measures will be used to assess association and effect sizes will be calculated with Cramer’s V to indicate the strength of association. Based on this information we will make recommendations for data collection using MTurk, including best practices, cautions, and the situations where it would be appropriate to use.

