### Approach to aim 2: evaluate and refine an impact subclassification scheme for chronic pain

In 2014 the NIH RTF recommended stratifying CLBP by its impact on patients’ lives according to pain intensity, pain interference with normal activities, and functional status [11]. The RTF’s proposed ISS sums the raw scores from 9 of the PROMIS-29 items covering physical function, pain interference, and pain intensity. The result is a total score with a possible range from 8 (least impact) to 50 (greatest impact) [11]. The NIH RTF allocated approximately equal percentages of individuals into three categories for the ISS: 8–27 (mild), 28–34 (moderate), and 35–50 (severe). We will estimate the percentages in these three ISS categories in each of our datasets. In addition, we will estimate internal consistency reliability and construct validity using Spearman rank-order and product-moment correlations between the ISS and variables with which it is hypothesized to be associated—e.g., healthcare utilization, worker productivity, and mood (depression and anxiety). We will also examine the correlations of the ISS with the ODI and RMDQ.

Further, we will evaluate responsiveness to change in the ACT dataset, MTurk and KnowledgePanel data using ANCOVA with the ISS as the dependent variable and a retrospective rating of change (Compared to 3 months ago, your low back pain is: *much worse, a little worse, about the same*, *a little better*, *moderately better, much better* and *completely gone*) as the independent variable. We will identify which ISS items are most responsive to change and use those reporting “about the same” to estimate test-retest reliability. The components that make up the ISS may differ by individual characteristics such as demographics and length of time patients have had chronic pain. We will examine whether low ISS scores are driven by pain intensity and higher scores by interference and/or physical function (similar to the structure of the Graded Chronic Pain Scale [21]), or if individuals’ scores or ISS categories are being driven mostly by (or by some particular pattern across) pain intensity, pain interference, or physical function. We will compare the grades of chronic pain based on the most well-studied and validated impact stratification scheme, the Graded Chronic Pain Scale [21, 24–30], to the range of ISS to see what this comparison offers in terms of appropriate ISS cut-points.

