Whereas this study offers several benefits to chronic pain researchers, it also faces challenges. The reliability and validity of the crosswalks between different measures generated by this study will be limited by the nature of the measures and the empirical associations we observe in the datasets analyzed. If the measures tap into different constructs, linking will not solve those differences. The ISS as proposed by the NIH Task Force may not capture the appropriate dimensions of chronic pain impact, or the dimensions that best define useful subgroupings (i.e., groupings of chronic pain patients with levels of condition severity and outcomes more homogenous than seen in chronic pain patients overall). Our use of MTurk as a data collection platform for intermediate analyses may generate samples that are different enough from those seen nationally that our estimated relationships will not hold up in the final national sample analyses.

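### Aim 3 compares relationships between MTurk and KnowledgePanel by correlations alone and does not carry the direct check of the links into the MTurk recommendation

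*Protocol article*

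**What the plan says.** The Aim 3 section lists what will be compared between MTurk and KnowledgePanel. One item is "relationships (correlations) seen between key variables", so relationships are equated with correlations. The method follows: "We will calculate and compare Spearman rank-order and product-moment correlations between key variables across data sources". The other statistical comparisons look at one variable at a time. They include "proportions with different levels of the ISS, and PROMIS-29 scale scores", outcome effect sizes, chi-square tests, and for means: "Student’s t-tests will be used for continuous outcome and demographic variables". The section then concludes: "Based on this information we will make recommendations for data collection using MTurk". It names no comparison of slope, intercept or prediction error.

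Elsewhere the article does more. The Aim 1 section compares PROMIS scores estimated from the ODI and RMDQ with observed scores in independent samples, including the new MTurk and KnowledgePanel data, at group and individual level. It names mean error and root-mean-squared error (RMSE) for the prediction models. The Aim 2 section gives ISS category percentages per dataset and sets Graded Chronic Pain Scale (GCPS) grades against the ISS: "to the range of ISS to see what this comparison offers in terms of appropriate ISS cut-points". The KnowledgePanel section says the panel will cross-validate all study results, without stating a criterion.

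**The concern.** Aims 1 and 2 do not deliver a correlation. They deliver a conversion (the PROMIS score expected at a given ODI or RMDQ score) and cut-points (the ISS values that separate impact groups). Both depend on the location and scale of the link, which a correlation discards. Pearson's r is unchanged by a shift or a positive linear rescale, and Spearman's by any increasing transformation. Correlations can also disagree when the link is identical, if one sample is more homogeneous.

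The mean and proportion comparisons do react to shifts. But MTurk is a convenience sample, so a difference in means may reflect who took part or a different score at the same ODI value. Advice on whether MTurk suits linking or cut-point work needs that distinction. The Discussion shows that the authors see the general risk, that "our estimated relationships will not hold up in the final national sample analyses".

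**Working it through.** **The plan's own precision figure.** The Sample sizes section gives standard errors of correlations of 0.07, 0.06 and 0.05 at n = 200, 300 and 400. With SE = 1/√n these are 0.0707, 0.0577 and 0.0500, so the figures reproduce. At the target of 1500 per source, SE = 0.026, and the SE of a difference of two Fisher z values is √(2/1497) = 0.037. This precision does not help here, because the expected difference in r under a pure shift or rescale is zero.

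**Assumptions (none are in the document).** PROMIS pain interference mean 55 and SD 8; ODI mean 25 and SD 16; r = 0.80. Then slope = 0.80 × 8/16 = 0.4 and residual SD = 8 × √(1 − 0.64) = 4.8. The sizes of shift and rescale are also assumed.

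1. *Shift.* MTurk PROMIS is 3 points higher at every ODI score. r stays at 0.80. Every converted score is off by 3 points, and 3/8 = 0.375 SD.
2. *Rescale.* MTurk ODI scores are compressed by 20% about the mean, so ODI SD = 12.8 and slope = 0.4/0.8 = 0.5. r = 0.5 × 12.8/8 = 0.80, unchanged. Converted scores differ by (0.5 − 0.4) × 20 = 2 points at 20 ODI points either side of the mean.
3. *Shift plus case mix.* MTurk participants are 7.5 ODI points milder, with the 3-point shift. MTurk PROMIS mean = 55 − 0.4 × 7.5 + 3 = 55.0, SD = √(6.4² + 4.8²) = 8.0 and r = 6.4/8 = 0.80, all equal to KnowledgePanel. The PROMIS t-test and the correlation show nothing. Only an ODI difference appears, and it reads as milder severity.
4. *Same link, different spread.* Table 1 gives average-pain SDs of 1.8 (CERC) and 2.2 (existing MTurk sample with CLBP), a ratio of 0.818. Suppose predictor SDs differed in that ratio, and take the ISS–ODI Spearman value of 0.81 from the Background as a working r. Then r in the narrower sample = 0.81 × 0.818/√(0.663² + 0.344) = 0.663/0.885 = 0.75. The Fisher z difference is 1.127 − 0.970 = 0.157, about 4 SE at 1500 per source. A sound link would look as if it had failed.

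**What the Aim 1 error measures would show.** In SD units at r = 0.81, RMSE with no difference is √(1 − 0.656) = 0.59. A 0.3 SD shift moves mean error from 0 to 0.30 and RMSE to √(0.344 + 0.09) = 0.66. A rescale of 1.3 leaves mean error at 0 and moves RMSE to √(0.3² × 0.656 + 1.3² × 0.344) = 0.80. These measures see what the correlation does not.

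**What a direct comparison could detect.** The SE of a platform term is about 4.8 × √(2/1500) = 0.175 point. With 80% power the detectable shift is about 2.8 × 0.175 = 0.49 point. This assumes unweighted data, full target samples and similar ODI distributions.

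**The case against.** The strongest reply is that crosswalk replication is not judged in Aim 3. The Aim 1 section tests it in KnowledgePanel with the right statistics. That stands. A reader might infer that a biased crosswalk could pass through the study as fully replicated. The documents do not support this, because comparing estimated with observed scores would expose it.

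Two supporting readings also go too far. The statement about using MTurk data to "see whether these estimates hold up in other samples" concerns estimates carried from the existing datasets to MTurk, not from MTurk to KnowledgePanel. The risk named in the Discussion concerns the final national analyses, which for crosswalks Aim 1 tests directly.

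It can also be said that the marginal comparisons would catch a plain shift. At 1500 per source the t-test has over 99.9% power at d = 0.30, and a PROMIS difference without a matching ODI difference would hint at the link. This holds when case mix is equal. Once case mix differs, as in the third example, the shift can be hidden or read as severity, and nothing in the section sets the two comparisons against each other.

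For Aim 2, the KnowledgePanel section commits to cross-validation, and the panel is to repeat the measures in the new MTurk survey. So it would be wrong to say that nothing is planned for the ISS; what is absent is a criterion.

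Finally, an article leaves much to a fuller plan. Here, however, the article names its measure of relationships, and that measure does not suit the use made of it.

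**Conclusion.** The point holds as a limited weakness in Aim 3. Its only stated comparison of relationships is insensitive to the differences that matter for conversions and cut-points, and it can signal failure when only spread differs. The accompanying marginal comparisons mix case mix with link differences. The accuracy results that would settle the matter for crosswalks exist under Aim 1 but are not brought into the MTurk recommendation. For ISS cut-points against GCPS grades, cross-validation is promised without saying what would count as agreement.

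The behaviour of correlations is algebra and needs no assumption. The sizes shown (3 points or 0.375 SD; 2 points; 0.81 falling to 0.75) rest on assumed shifts, scales and SDs, since the document gives none. They show what could be missed or misread, not a bias that is expected. No sample size or power figure is challenged.

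**What to change.** In the Aim 3 section:

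- Keep the correlations as description.
- For each key pair (PROMIS-29 scales and ISS, each on ODI and RMDQ), fit one regression to the pooled new MTurk and KnowledgePanel data with the measure, platform, and platform-by-measure. Report the MTurk minus KnowledgePanel difference in expected score, with confidence interval, at a low, middle and high value. Alternatively, report the mean error and RMSE of the MTurk-derived link in KnowledgePanel, drawing on the Aim 1 work.
- Report the ISS value at each GCPS grade boundary by platform, using the same rule on both.
- State that the relationship part of the MTurk recommendation rests on these results.

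The platform term measures a difference at equal scores and does not explain it. Aim 1 already plans to check whether the prediction equation varies by patient characteristics and over time, and platform can be added to that list. The cost is a few sentences and a few regressions. No new data are needed, provided the ODI, RMDQ and GCPS are in both surveys, as the article foresees.

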### Sample sizes

For confirmatory factor analysis, rules of thumb have been offered about the minimum number of subjects per each parameter to be estimated (e.g., at least 10 subjects per parameter [82]). If a measure is to be used in a specific subgroup (e.g., those with longer duration of pain), then a sufficient sample size is needed to represent that subgroup. It has been suggested that sample sizes of 200 are needed for the Rasch model for dichotomous items [83]. At this sample size, SEs of item thresholds are in the range of 0.14 to 0.21 (based on [2/(square root of n)] < SE < [3/(square root of n)], where n is the sample size). For graded-response models, a sample size of 500 is recommended [83]. Although at least 500 is desirable, a smaller sample could still provide useful information, depending on the properties and composition of the scale. In general, the ideal situation is to have adequate representation of respondents for each combination of possible response patterns across a set of items—something that is rarely achieved. It is important, however, to have at least some people respond to each of the categories of every item. We will have data with large numbers of CLBP patients from three existing studies available with wide distributions of item responses that will make possible the proposed initial analyses. The standard errors of correlations are 0.07, 0.06 and 0.05 for sample sizes of 200, 300 and 400, respectively. Logistic and other types of regression equations have lower sample size requirements. To ensure that we have sufficient power for subgroup analyses, sufficient representation of all possible response patterns, and a nationally representative sample sufficient for validation of all results, our MTurk data collection and KnowledgePanel sample will aim for sample sizes of 1500 each.

## Discussion

The intent of Aims 1 and 2 is to allow direct comparison of results across past and future studies of CLBP. These comparisons will help us to understand why similar studies yield different results, and to determine the relative effectiveness of all pharmaceutical and nonpharmacologic interventions for chronic pain, even if they were not directly compared in a trial.

In particular, the results of Aim 1 will enable side-by-side comparisons among studies using different measures. In addition, these links and crosswalks will aid in the interpretation of the results of meta-analyses, and enable the harmonization required for detailed individual patient data (IPD) meta-analyses [16, 17]. The chronic pain stratification results of Aim 2 will enable the examination of baseline sample characteristics and to incorporate differences seen there when comparing across studies. When individual patient data are available, samples can be balanced by pain impact category through case-mix adjustment [33] or weighting, and subgroup analyses would be possible using methods such as IPD meta-analysis or simulation modeling. For future trials, targeting patients at the same chronic pain impact level will enhance trial efficiency by reducing patient heterogeneity, and researchers could later report on heterogeneity of treatment effect (HTE) using the groupings defined by this stratification. Finally, stratification and knowing the results of studies by chronic pain subgroup will allow interventions to be targeted to the patient subgroups where they will be the most effective.

The results of Aim 3 will produce needed information about the data quality available from the MTurk platform and provide guidance of how to ensure that quality and its limits. We will also provide information on its efficiency in time and cost for chronic pain data collection.

Whereas this study offers several benefits to chronic pain researchers, it also faces challenges. The reliability and validity of the crosswalks between different measures generated by this study will be limited by the nature of the measures and the empirical associations we observe in the datasets analyzed. If the measures tap into different constructs, linking will not solve those differences. The ISS as proposed by the NIH Task Force may not capture the appropriate dimensions of chronic pain impact, or the dimensions that best define useful subgroupings (i.e., groupings of chronic pain patients with levels of condition severity and outcomes more homogenous than seen in chronic pain patients overall). Our use of MTurk as a data collection platform for intermediate analyses may generate samples that are different enough from those seen nationally that our estimated relationships will not hold up in the final national sample analyses.

## Data Availability

This study will use data from a variety of datasets. Some of these are existing and publicly available and we will provide links to those. Others of the datasets are not publicly available due to this provision not being included in participants’ consent forms but are available from the corresponding author on reasonable request.

## Abbreviations

ACT: Assessment of Chiropractic Treatment for Low Back Pain trial
CERC: RAND Center of Excellence for the Appropriateness of Care
CFI: Comparative fit index
CLBP: Chronic low back pain
CNP: Chronic neck pain
IRT: Item response theory
ISS: Impact Stratification Score
MTurk: Amazon Mechanical Turk
NDI: Neck Disability Index
NIH: National Institutes of Health
NPS: National Pain Strategy
ODI: Oswestry Disability Index
PRO: Patient-reported outcome
PROMIS: Patient-Reported Outcomes Measurement Information System
RMDQ: Roland-Morris Disability Questionnaire
RMSEA: Root mean square error of approximation
RTF: Research task force
SRMR: Standardized root means square residual
